### Definitions

#### Comparator Group (Standard of Care)

Currently, APRI and FIB-4 scores are not routinely reported anywhere in Australia. Prior to the intervention, blood tests will be reported per standard of care. APRI and FIB-4 scores will be calculated automatically by the pathology service from the start of the study but will not be reported to ordering clinicians until the intervention period. FibroScans are requested through a paper-based referral form by general practitioners or specialists, which is then faxed to the hospital for triage and booking.

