#### Intervention (In Addition to Standard of Care)

St Vincent’s Pathology automatically calculates and reports APRI and FIB-4 scores if platelet count, alanine transferase (ALT) level, and AST level are requested together in a single blood test by primary care physicians. This is provided free of charge. The result will be reported to the requesting primary care physician (both in paper format and online), along with a brief interpretation of the APRI and FIB-4 results, their relevance to liver cirrhosis screening, and a web link for further web-based information. No additional testing or appointments are scheduled as part of this study in addition to the standard of care.

Two separate pathways will be used by St Vincent’s Pathology to notify clinicians of our new APRI and FIB-4 reporting format approximately 1 month prior to the commencement of the intervention period. (1) The St Vincent’s Pathology standard liver function test result report will include a comment stating that APRI and FIB-4 scores will be reported as of the date of project commencement. (2) There will be a new banner included on the St Vincent’s Pathology website notifying clinicians of the availability of automatic reporting of APRI and FIB-4 scores on blood test events and the date that this reporting will commence. This will have a web link to further information on the APRI and FIB-4 score, as well as information about chronic liver disease.

The additional information on the website includes (1) how APRI and FIB-4 are calculated and how it is used, (2) how to interpret the APRI and FIB-4 result, (3) what further tests would be recommended if someone has an abnormal APRI result, (4) further general information about chronic liver disease and liver cirrhosis, and (5) a link to a web-based referral form for the St Vincent’s Hospital FibroScan service to book a confirmatory FibroScan to determine whether the patient has liver cirrhosis.

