### Recruitment

All individuals aged 18 years and older who have liver function tests and full blood count requested by a community-based health worker and performed at St Vincent’s Pathology between August 1, 2023, and July 31, 2024, will be recruited. There will be no active recruitment of participants for this study.

This study is an evaluation of a health system–wide introduction of routine reporting of APRI calculation, information on liver cirrhosis, and a web link through St Vincent’s Pathology to improve the quality of care for people with liver disease; therefore, no individuals will individually consent to participate. No personally identifying information will be collected and all data supplied to the research team will be deidentified by St Vincent’s Pathology and transient elastography booking and reporting teams, respectively. Variables including 10-year age category, sex, and postcode will be collected as part of the study but will not allow identification of individuals, as they are broad categories expected to contain more than 1000 persons per strata per month during the study period.

The exclusion criteria of this study include children aged 18 years or younger and blood tests performed during a hospital inpatient stay, or requested by hospital outpatient service, defined by St Vincent’s Pathology records (blood collection site).

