### Study Timeline

#### Preintervention Period

Between August 1, 2023, and January 31, 2024, St Vincent’s Pathology will prospectively collect data on all ALT, AST, and platelet count test results conducted, and APRI and FIB-4 scores will be automatically calculated by the St Vincent’s Pathology data management system, but not reported to the ordering clinician. These data will be prospectively collected from St Vincent’s Pathology by a member of the study team, along with exposure variables outlined above. During the same time period, outcome measures per month will be prospectively collected from the St Vincent’s hospital electronic medical records by a member of the research team (number of FibroScan referrals, number [proportion] of scheduled FibroScan appointments attended, number [proportion] diagnosed with cirrhosis, and number [proportion] linked to specialist care).

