### Statistical Analysis Plan

#### Outcome Measures

Data will be analyzed per test event and per individual tested.

Primary outcomes of this study include the number of APRI and FIB-4 scores calculated on blood test events conducted during the study period, overall and per month; the number (proportion) of APRI scores that are greater than 1.0 and FIB-4 scores that are greater than 2.67; number of FibroScan referrals overall and per month, operationalized as number of completed FibroScan referrals generated online using the recommended St Vincent’s Pathology FibroScan referral link on the request slip, or St Vincent’s Pathology APRI or FIB-4 calculation web page referral form link; number of individuals with an APRI greater than 1.0 or FIB-4 score greater than 2.67 who undergo a FibroScan test at St Vincent’s Hospital Melbourne overall and per month; proportion of individuals with an APRI greater than 1.0 or FIB-4 score greater than 2.67 who undergo a FibroScan test at St Vincent’s Hospital Melbourne; the number of individuals per month who undergo FibroScan at St Vincent’s Hospital Melbourne who have cirrhosis diagnosed (liver stiffness measurement >12.5kPa); the number (proportion) of individuals with an APRI greater than 1.0 or FIB-4 score greater than 2.67 who have cirrhosis confirmed by FibroScan; the number (proportion) of individuals with etiology-specific cirrhosis range FibroScan results that are referred to the specialist liver clinic; and the number (proportion) of individuals with etiology-specific cirrhosis range FibroScan results that attend to the specialist liver clinic appointment.

The secondary outcomes of this study include the number (proportion) of individuals, stratified by age category, sex, and postcode who have elevated APRI greater than 1.0 and FIB-4 score greater than 2.67, attend the FibroScan clinic for further testing, have etiology-specific cirrhosis range FibroScan scores (kPa), and attend a liver specialist clinic appointment.

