### Sample Size Justification

We have conducted a preliminary analysis of the number of AST and platelet count testing events that were performed at St Vincent’s Pathology over a 12-month period (2019). These data showed approximately 11,000 people known to St Vincent’s hospital clinics, and a further 4400 people in the community that had AST and platelet count testing events, that would have allowed APRI calculation to be performed, proving the feasibility of reaching large numbers within the community for cirrhosis screening.

For the comparison of rate of referral for FibroScan before and after the intervention, we estimate that we will be powered to detect a 10% difference in rates of FibroScan referral before and after the intervention. For the logistic regression analyses to determine the difference in proportion of APRI scores leading to referral before and after providing cirrhosis information and FibroScan referral link information (overall and by subgroup), and for determining the proportion of FibroScan referrals that are attended (overall and by subgroup), we are powered to detect a 5% or greater difference between the intervention and historical control groups with power 90% and a sample size of 1100 per subgroup. The above numbers of more than 15,400 individuals having APRI calculations within 12 months suggest that we will be adequately powered to explore our end points including stratified by sex, urban versus rural place of residence, age category, socioeconomic quartile of place of residence, and indication for FibroScan (all of which are expected to have >1000 individuals in each subgroup).

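### The compared monthly FibroScan referral and cirrhosis-diagnosis counts are not tied to the people the intervention reaches, and referrals are not defined alike in the two phases

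*Protocol article*

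**What the plan says.** **Who is exposed.** Under Intervention, "The result will be reported to the requesting primary care physician (both in paper format and online"). Recruitment limits the study to adults with tests ordered by a community-based health worker, and excludes "blood tests performed during a hospital inpatient stay, or requested by hospital outpatient service".

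**What is counted before the intervention.** Under Comparator Group, "FibroScans are requested through a paper-based referral form by general practitioners or specialists". Under Preintervention Period, "outcome measures per month will be prospectively collected from the St Vincent’s hospital electronic medical records by a member of the research team". These measures include the number of FibroScan referrals and the number with cirrhosis. No restriction by requester, or to people with an eligible blood test, is stated.

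**What the outcomes are.** Outcome Measures lists as primary "the number of individuals per month who undergo FibroScan at St Vincent’s Hospital Melbourne who have cirrhosis diagnosed" (stiffness above 12.5 kPa), again without restriction. The same section defines FibroScan referrals as completed online referrals through the pathology service's link or web page form. Intervention Period says this link is separate from the fax form, so that referrals prompted by the scores can be measured. Other primary outcomes in the list are limited to individuals with APRI above 1.0 or FIB-4 above 2.67.

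**What is compared, and the sizing.** Analysis Methods compares the number of referrals after the intervention with the number before, as a time series interrupted on February 1, 2024. Sample Size Justification says "we estimate that we will be powered to detect a 10% difference in rates of FibroScan referral before and after the intervention".

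**The concern.** A pre-post comparison needs one quantity, measured the same way in both phases, in the people the intervention can affect. Two things go wrong here.

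- **Scope.** The hospital's FibroScan clinic serves specialist requesters and may scan people whose blood tests were never eligible. The score report is not directed at these scans, yet the all-clinic cirrhosis count and the pre-intervention referral count include them. They dilute a relative effect. In a single-arm design they also let a change in unrelated clinic activity look like a programme effect, or hide one.
- **Definition by phase.** The stated referral definition counts a route that is not described before the intervention. The count it is compared with consists of paper and fax referrals.

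Referral and cirrhosis-diagnosis rates are the headline comparisons in the abstract, so the main conclusions depend on both points.

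**Working it through.** **1. The plan's own figure.** The 10% in Sample Size Justification has no baseline count, power or scale (absolute or relative), so it cannot be reproduced. The 90% power in that section belongs to a different comparison (a 5% difference, 1100 per subgroup). Below, 10% is taken as relative and 90% power is assumed.

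**2. The referral definition, phase by phase.** Before the intervention, referrals arrive on paper by fax and no link route is described. From February 1, 2024 the link runs beside the fax form. Two readings are possible:
- Link referrals in both phases: the baseline is zero in all six months. A ratio is undefined and there is no pre-intervention level or trend to interrupt.
- All hospital-record referrals before, link referrals after: the two phases count different things.

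Illustration with assumed inputs: 600 pre-intervention referrals, half from reachable people, a true 30% rise among them, all extra referrals through the link, fax volume unchanged. Extra referrals = 600 × 0.5 × 0.30 = 90.

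| Count | Before | After | Ratio |
|---|---|---|---|
| Link only | 0 | 90 | undefined |
| Fax before, link after | 600 | 90 | 0.15 |
| Any route, whole clinic | 600 | 690 | 1.15 |
| Any route, reachable people | 300 | 390 | 1.30 |

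The second row shows a fall although referrals rose. This is not dilution. If fax users switched to the link, the link count would instead include referrals that would have happened anyway.

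**3. Attenuation of an all-clinic count.** Let s be the share of the pre-intervention count from reachable people and e the relative effect among them. If the rest is unchanged, overall effect = s × e. The overall effect is at least 10% only if s ≥ 10%/e:

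| e | 10% | 15% | 20% | 30% | 50% | 100% |
|---|---|---|---|---|---|---|
| minimum s | 100% | 67% | 50% | 33% | 20% | 10% |

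The same formula holds for the cirrhosis count, with s then being the share of diagnoses.

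**4. Cost in precision.** Poisson comparison, two-sided 0.05, ignoring trend and autocorrelation: pre-intervention count N = (1.960 + 1.282)² × (1 + 1/RR) / (ln RR)². For RR = 1.10, N ≈ 2209. If e is exactly 10%:

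| s | All-clinic RR | All-clinic N needed | Clinic total giving 2209 reachable (2209/s) |
|---|---|---|---|
| 0.75 | 1.075 | 3878 | 2945 |
| 0.50 | 1.050 | 8618 | 4418 |
| 0.25 | 1.025 | 34,046 | 8836 |

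With a larger effect (e = 30%) and 600 pre-intervention clinic referrals, power for the all-clinic versus the restricted count is 0.96 vs 0.99 (s = 0.75), 0.71 vs 0.93 (s = 0.50) and 0.25 vs 0.68 (s = 0.25). Restriction helps at each of these shares even though it reduces the count.

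**5. Unrelated change.** If activity outside the reachable group changes by c, the clinic total moves by (1 − s) × c. With s = 0.50 and c = 20%, that is 0.50 × 20% = 10%, with no programme effect at all.

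**The case against.** **The link definition already isolates score-driven referrals.** It does so after the intervention starts, and the separate link is useful for that. It supplies no comparator, and Analysis Methods calls for one. It does not touch the cirrhosis count. What stands is that, under the link definition, specialist fax requests do not dilute the referral outcome. The fault there is the change of definition between phases.

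**Restricted outcomes already exist.** This is correct. Scans undergone and cirrhosis confirmed are also listed for people with an elevated score, and Results says linkage to referral and attendance data is under way. A reader might infer that the plan holds only clinic-wide totals, and it does not. The unrestricted cirrhosis count is still primary beside them.

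**Some specialists may be reached.** Recruitment speaks of community-based health workers and the website banner addresses clinicians generally. A primary care physician who sees a raised score may also refer to a specialist, who then requests the scan. That is a programme effect, so limiting the outcome to primary-care-requested scans would remove part of it. This objection stands and shapes the fix.

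**The article is condensed.** The point does not rest on omitted detail. The stated referral definition and the stated pre-intervention source do not fit each other.

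**Conclusion.** The point holds. The all-clinic cirrhosis count and the pre-intervention referral count do not match the population that receives the scores, and the referral outcome has either a zero baseline or a different definition in each phase.

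The size of the attenuation is s × e, and the documents give neither. A reader might infer that a true effect will be diluted below 10%. That does not follow: it is certain only if the true effect is itself about 10%, whereas a 50% effect at a 50% reachable share still appears as 25%. Nor does the plan say that its 10% refers to the mixed clinic rate; it does not say which referrals the figure concerns. The 2019 counts (about 11,000 people known to the hospital's clinics against 4400 in the community, or 11,000/15,400 = 71%) describe blood tests, not FibroScan referrals, so they do not supply the missing share.

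The figures above assume a relative effect, Poisson counts, no trend, and no change outside the reachable group except in step 5.

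**What to change.** - In Preintervention Period, Outcome Measures and Analysis Methods, define the compared referral and cirrhosis-diagnosis counts identically in both phases: by any referral route (fax or link), in individuals with an eligible community-ordered St Vincent's Pathology test, identified through the linkage described in Results.
- Report these counts split by requester type and by route. Do not exclude specialist-requested scans in eligible people.
- Keep all-clinic totals and link-only referrals as separate descriptive series.
- In Sample Size Justification, restate the 10% for the restricted count and give its baseline, scale (absolute or relative) and power.

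The cost is a change of outcome wording and one extra field, requester type, taken from existing referral forms. Counts will be smaller and the stated detectable difference less favourable.

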#### Intervention (In Addition to Standard of Care)

St Vincent’s Pathology automatically calculates and reports APRI and FIB-4 scores if platelet count, alanine transferase (ALT) level, and AST level are requested together in a single blood test by primary care physicians. This is provided free of charge. The result will be reported to the requesting primary care physician (both in paper format and online), along with a brief interpretation of the APRI and FIB-4 results, their relevance to liver cirrhosis screening, and a web link for further web-based information. No additional testing or appointments are scheduled as part of this study in addition to the standard of care.

Two separate pathways will be used by St Vincent’s Pathology to notify clinicians of our new APRI and FIB-4 reporting format approximately 1 month prior to the commencement of the intervention period. (1) The St Vincent’s Pathology standard liver function test result report will include a comment stating that APRI and FIB-4 scores will be reported as of the date of project commencement. (2) There will be a new banner included on the St Vincent’s Pathology website notifying clinicians of the availability of automatic reporting of APRI and FIB-4 scores on blood test events and the date that this reporting will commence. This will have a web link to further information on the APRI and FIB-4 score, as well as information about chronic liver disease.

The additional information on the website includes (1) how APRI and FIB-4 are calculated and how it is used, (2) how to interpret the APRI and FIB-4 result, (3) what further tests would be recommended if someone has an abnormal APRI result, (4) further general information about chronic liver disease and liver cirrhosis, and (5) a link to a web-based referral form for the St Vincent’s Hospital FibroScan service to book a confirmatory FibroScan to determine whether the patient has liver cirrhosis.

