### Primary Outcome Measurement

The primary outcomes prospectively commenced on August 1, 2023, for 6 months before intervention and will continue until the conclusion of the intervention period on July 31, 2024. The impact of the intervention will be determined by comparing primary outcome measures during the intervention period to the 6 months prior to the intervention (standard of care).

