#### Intervention Period

From February 1, 2024, to July 31, 2024, St Vincent’s Pathology will commence inclusion of automatic calculation of APRI and FIB-4 score reporting on all pathology blood testing events where an AST, ALT, and platelet count are ordered. St Vincent’s Pathology will provide for these testing events: (1) the APRI result, (2) the FIB-4 result, (3) an explanation of what APRI and FIB-4 measure and what cutoffs are used to define cirrhosis, and (4) recommendations for further investigation of elevated APRI or FIB-4 with transient elastography (FibroScan) and performance of a liver disease screen if underlying liver disease is not known. In addition, a web link to the St Vincent’s Pathology website for liver disease and cirrhosis information page will be included on all blood test reports where APRI and FIB-4 are calculated, with a provided URL link to a unique St Vincent’s Hospital FibroScan referral form. This link will be distinct from the standard fax-based St Vincent’s FibroScan referral form to allow measurement of referrals specifically generated in response to St Vincent’s Pathology APRI or FIB-4 score calculations during the study period.

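### The two phases share no calendar month, so season is aliased with the intervention for the outcomes compared before and after, and January 2024 is not pure standard of care

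*Protocol article*

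**What the plan says.** All places are in the protocol article.

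- **Windows.** Preintervention Period: "Between August 1, 2023, and January 31, 2024". Intervention Period: "From February 1, 2024, to July 31, 2024". Study Design describes a single-arm pilot.
- **Comparator.** Primary Outcome Measurement judges impact against the whole of the preceding six months, labelled standard of care. Analysis Methods places the interruption of the time series at February 1, 2024 and names no transition period.
- **Notification.** Intervention (In Addition to Standard of Care) has clinicians told "approximately 1 month prior to the commencement of the intervention period". The standard liver function report "will include a comment stating that APRI and FIB-4 scores will be reported as of the date of project commencement". A banner also goes on the pathology website: "This will have a web link to further information on the APRI and FIB-4 score, as well as information about chronic liver disease". The website information includes score interpretation, recommended further tests and "a link to a web-based referral form for the" hospital's FibroScan service.
- **Referral outcome.** Outcome Measures counts FibroScan referrals completed online through the new links. Intervention Period says that this form is kept distinct from the fax form so that referrals prompted by the scores can be measured. Comparator Group describes preintervention referral as paper and fax. Preintervention Period lists the number of FibroScan referrals from hospital records without restricting the route.
- **Limitations.** Strengths and Limitations mentions neither season nor anticipation.

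**The concern.** A before-after comparison in one arm attributes to the intervention whatever else differs between the two periods. Here one period is late winter to midsummer in Victoria, including the year-end holidays, and the other is late summer to midwinter. Testing volume, clinic capacity and attendance may all differ between those halves of the year. Because each calendar month is seen once only, the data contain no information on what February to July would have looked like without the intervention, beyond extrapolation from other months.

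The last baseline month has a second problem. Reports change and information is advertised from about January 1, 2024, and information and a referral link are themselves components of the screening package. Comparator Group says that blood tests are reported per standard of care before the intervention, which sits uneasily with a comment added to the standard report in that period. January also adjoins the interruption, where a segmented model is most sensitive.

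At stake is how far a change in scans, diagnoses, attendance or linkage can be credited to automated reporting.

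**Working it through.** **The plan's own figures.** The protocol gives no size for season or anticipation, so there is no figure to reproduce. Sample Size Justification mentions a detectable 10% difference in referral rates without a baseline rate or power. That claim cannot be reproduced, and nothing below rests on it.

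**1. Overlap.** Pre: Aug, Sep, Oct, Nov, Dec, Jan. Post: Feb, Mar, Apr, May, Jun, Jul. Months in common: 0. A design matrix of 12 month indicators has rank 12, and the rank stays 12 when phase is added, so phase is fully aliased with calendar month. A single annual sine/cosine pair alone explains 83% of the variance of the phase indicator.

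**2. Scale of a seasonal effect (assumed).** Take a base of 100, no true effect and an annual sine wave of amplitude 10%. In the worst timing, the mean of six consecutive months departs from 100 by 10 × 1/(6 sin 15°) = 6.44.
- Low half first: (106.44 − 93.56)/93.56 = +13.8%.
- High half first: (93.56 − 106.44)/106.44 = −12.1%.
- The level change in a segmented model (intercept, time, phase, time after) ranges from −13.5 to +13.5 per 100.

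These are extremes over the timing of the peak. They apply to monthly counts with an appreciable baseline.

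**3. January 2024.** Notification at about January 1 touches 1 of 6 baseline months. Number the months 1 to 6, with mean 3.5 and sum of squared deviations 17.5. The least-squares weight of month 6 in the level projected to month 7 is

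1/6 + (7 − 3.5)(6 − 3.5)/17.5 = 0.167 + 0.500 = 0.667.

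In a simple mean the weight is 1/6 = 0.167. With an assumed true step of +10 on a base of 100:

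| January shift (assumed) | Segmented level change | Pre-post change |
|---|---|---|
| +10 (early referral) | 10 − 6.67 = 3.3 | (110 − 101.67)/101.67 = 8.2% |
| 0 | 10 | 10% |
| −10 (deferral) | 10 + 6.67 = 16.7 | (110 − 98.33)/98.33 = 11.9% |

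The bias can go either way, and it is much larger in a segmented model with a baseline slope than in a mean comparison.

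**4. Price of leaving January out.** The variance of the level change, in units of the residual variance, is the pre-phase projection variance plus the post-phase variance at its first month.
- All 12 months: (1/6 + 3.5²/17.5) + (1/6 + 2.5²/17.5) = 0.867 + 0.524 = 1.390.
- Without January (months 1 to 5, mean 3, sum of squares 10): (1/5 + 4²/10) + 0.524 = 2.324.
- Standard-error ratio: √(2.324/1.390) = 1.29.

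**5. Can the 12 months be adjusted for season?** Adding one annual sine/cosine pair raises the variance from 1.390 to 5.871, a standard-error ratio of 2.05, with 6 residual degrees of freedom (12 − 6 parameters). It also assumes that season is a single smooth wave.

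**6. What February to July 2023 would add.** With 18 months, month indicators plus phase have rank 13, so phase becomes estimable. The same segmented model with one harmonic has level-change variance 2.125, a ratio of √(2.125/1.390) = 1.24 to the unadjusted 12-month model, with 12 residual degrees of freedom (18 − 6). One limit remains. With full month indicators, a linear trend and phase cannot both be estimated: numbering the months 0 to 17, time − 12 × phase takes the same value in the same calendar month of both years. The rank stays 13 when trend is added.

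**The case against.** The strongest reply is the unique web form. Link-based referrals have a near-zero baseline by design, so neither a holiday dip nor a seasonal swing could create them. This stands. A reader might infer that the before-after comparison is the only evidence of effect, or that a 10% seasonal swing would match the 10% difference in referral rates that the plan says it can detect. The documents support neither for the link-defined outcome. The open question is whether the form was live in January, since no go-live date is given.

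Second, for outcomes expressed as proportions, such as those scanned among people with elevated scores, seasonal test volume largely cancels. That stands too, although seasonal differences in clinic capacity and attendance do not cancel.

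Third, January clinicians received an announcement but no patient's score, so the effect may be small. This is fair, and the documents give no size. A reader might also infer that an exposed January can only bias the step toward zero. Clinicians told that scores arrive next month may equally wait, which would inflate it.

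Fourth, Analysis Methods names logistic regression as a time series analysis for referrals and does not state slope terms, so the 0.667 weight applies only if a linear segmented model with a baseline slope is fitted. Agreed.

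Finally, a sensitivity analysis or seasonal term can be left to an analysis plan not shown, and a pilot may be single-arm. Both are true. But the protocol itself fixes the windows, the comparator and the interruption date, and no later analysis confined to these 12 months can fully undo the aliasing.

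**Conclusion.** The point holds with limited reach. Season is aliased with phase for monthly FibroScans performed, cirrhosis diagnoses, attendance and linkage, and for referrals if all routes are counted. That follows from the stated dates and needs no assumption. It is of little consequence for link-based referrals, provided the form was not live in January.

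January 2024 is also not pure standard of care, because clinicians are notified in it. The direction of the resulting bias is open.

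The size of either effect is unknown. The ranges of −12.1% to +13.8% for season and ±6.7 per 100 for January rest on an assumed 10% amplitude and an assumed 10% January shift, the latter in a linear segmented model. They show sensitivity and do not predict the bias.

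A reader might look to specialist-requested referrals to the same clinic as a concurrent control. The documents do not support treating them as unexposed: the website banner is open to all clinicians, and the clinic's capacity is shared.

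**What to change.** 1. **Same-month history.** Extract existing monthly counts of FibroScan referrals, scans, cirrhosis-range results and clinic linkage, where retrievable, for at least February to July 2023. Compare February to July 2024 with those months as well as with the preceding six, and enter the longer series in the time series model. With only one extra half-year, represent season by a harmonic term if a trend is also fitted; more years would relax this. The 2019 preliminary analysis shows that past laboratory counts can be obtained. That booking and clinic counts can be obtained is an inference from their source in the hospital's electronic records.
2. **January 2024.** Keep it in the main analysis and prespecify a sensitivity analysis that treats it as a transition month and leaves it out. The 1.29-fold standard error in a 12-month segmented model is the reason to keep this as a sensitivity analysis.
3. **Referrals.** Report link-based and all-route referrals separately in both phases, and state when the web form went live.
4. **Limitations.** Name season and anticipation.

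The cost is one retrospective data pull with ethics notification and a little more analysis. The Results section puts the start of data analysis in August 2024, so all of this can be fixed before then.
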